## Abstract

**Background:**

There is good evidence that trauma-focused therapies for Post-Traumatic Stress Disorder are effective. However, they are not always feasible to deliver due a shortage of trained therapists and demands on the patient. An online trauma-focused Guided Self-Help (GSH) programme which could overcome these barriers has shown promise in a pilot study. This study will be the first to evaluate GSH against standard face-to-face therapy to assess its suitability for use in the NHS.

**Methods:**

The study is a large-scale multi-centre pragmatic randomised controlled non-inferiority trial, with assessors masked to treatment allocation. One hundred and ninety-two participants will be randomly allocated to receive either face-to-face trauma-focused cognitive behaviour therapy (TFCBT) or trauma-focused online guided self-help (GSH). The primary outcome will be the severity of symptoms of PTSD over the previous week as measured by the Clinician Administered PTSD Scale for DSM5 (CAPS-5) at 16 weeks post-randomisation. Secondary outcome measures include PTSD symptoms over the previous month as measured by the CAPS-5 at 52 weeks plus the Impact of Event Scale – revised (IES-R), Work and Social Adjustment Scale (WSAS), Patient Health Questionnaire-9 (PHQ-9), General Anxiety Disorder-7 (GAD-7), Alcohol Use Disorders Test (AUDIT-O), Multidimensional Scale for Perceived Social Support (MSPSS), short Post-Traumatic Cognitions Inventory (PTCI), Insomnia Severity Index (ISI) and General Self Efficacy Scale (GSES) measured at 16 and 52 weeks post-randomisation. Changes in health-related quality of life will be measured by the EQ-5D and the level of healthcare resource utilisation for health economic analysis will be determined by an amended version of the Client Socio-Demographic and Service Receipt Inventory European Version. The Client Satisfaction Questionnaire (CSQ) will be collected at 16 weeks post-randomisation to evaluate treatment satisfaction.

**Discussion:**

This study will be the first to compare online GSH with usual face-to-face therapy for PTSD. The strengths are that it will test a rigorously developed intervention in a real world setting to inform NHS commissioning. The potential challenges of delivering such a pragmatic study may include participant recruitment, retention and adherence, therapist retention, and fidelity of intervention delivery.

**Trial registration:**

ISRCTN13697710 registered on 20/12/2016.

## Background

Post-Traumatic Stress Disorder (PTSD) is a common mental disorder that may develop following exposure to exceptionally threatening or horrifying events. Characteristic symptoms include persistent intrusive recollections, avoidance of trauma-related stimuli, negative alterations in thoughts and mood and hyper-arousal [1, 2]. About 3% of the adult population suffer from current PTSD [3] and average symptom duration is normally prolonged in those who are untreated [4]. PTSD is associated with substantial co-morbidity [4–8] and significant economic burden [9, 10].

A number of psychological approaches have been developed to treat PTSD. Evidence suggests that the most effective approaches are trauma focused cognitive behavioural therapy (TFCBT), including trauma focused cognitive therapy, and eye movement desensitization and reprocessing therapy (EMDR) [11]. TFCBT typically involves some degree of structured exposure to and processing of traumatic memories and trauma reminders, alongside cognitive restructuring of dysfunctional beliefs about the meaning of the trauma. EMDR is a psychological therapy that involves exposure to unwanted and distressing memories whilst focusing on a bilateral stimulation. TFCBT and EMDR have become the treatments of choice for PTSD, recommended by clinical guidelines in the UK and internationally [12–14]. TFCBT protocols vary in the focus on exposure or cognitive interventions and differ slightly in the number of treatment sessions that are recommended. National Institute for Health and Care Excellence (NICE) recommend treatment of 8–12 sessions lasting 60–90 min for individuals who have experienced a single trauma, with a recommendation of more than 12 sessions in chronic, complex cases i.e. with multiple traumas.

Despite a growing consensus that trauma focused psychological therapies (TFPTs) represent the most effective way of treating PTSD, they are not always feasible to deliver. There remains a shortage of suitably qualified therapists to deliver these interventions and therefore, in many places, lengthy waiting times are common. If left untreated, PTSD is associated with functional and emotional impairment, reduced quality of life, a predisposition for the development of other psychiatric and physical illnesses, increased suicidal ideation, higher healthcare utilisation, and higher rates of alcohol abuse and dependence [15–21]. Current TFPT treatment requires a considerable commitment from the service user to attend weekly out-patient appointments on a regular basis over several months. Therapy can be difficult for some people to access, due to factors such as perceived stigma about attending mental health services, difficulty getting time off work, problems accessing or arranging suitable childcare and travel for people living in remote areas [22–24]. As a result of these and other factors, drop-out from TFPT interventions can be high [11].

Guided self-help (GSH) could offer a solution to these issues. GSH combines the use of self-help materials (e.g., a work-book, or a website), with regular guidance from a trained mental health professional and requires less therapist time than an equivalent therapist-administered treatment. There is good evidence of the efficacy of GSH in other mental health disorders [25]. In recognition of these findings NICE recommended that a randomised controlled trial (RCT) of GSH should be conducted to assess the efficacy and cost-effectiveness of guided self-help compared with trauma focused psychological interventions for mild and moderate PTSD [12]. If effective, GSH would offer a time-efficient treatment option with the potential to reduce waiting times and would be more accessible and less of a burden to participants. It is also likely that GSH would reduce intervention costs, and may lessen the burden of PTSD to the NHS and society.

Some of the authors (JB, CL, NR, NK) have systematically developed a novel, internet-based GSH programme for PTSD based on TFCBT. This was developed over a number of years following Medical Research Council (MRC) guidance for the development of a complex intervention [26] with significant input from PTSD sufferers and professional stakeholders. Intervention development work was completed between 2007 and 2010. A modelling phase included key stakeholders in focus groups and semi-structured interviews to inform the content, delivery and guidance of a GSH programme for PTSD. Data was analysed using qualitative methodology and used to inform the first prototype. The prototype was piloted twice with a total of 19 participants with PTSD and refined on the basis of qualitative and quantitative results. Quantitative results strongly supported the potential of the programme to effectively treat PTSD [27].

An interactive online version of the programme was produced through a Knowledge Transfer Partnership (KTP) between Health Care Learning Limited Ltd (HCL) and Cardiff University. The partnership combined HCL’s expertise in developing high quality internet-based programmes, with the academic team’s experience of developing and evaluating psychological interventions for PTSD. A pilot feasibility RCT of the intervention was completed between 2012 and 2014. Forty-two participants with mild to moderate PTSD after a single traumatic event were randomised to receive immediate GSH or delayed treatment [28].

Following GSH, PTSD sufferers’ symptoms improved by over 50% (completers only) and over 40% (intention to treat) with an average of 149 min of therapist input; effect sizes that compare favourably with those found for therapist-delivered TFPT. The treatment group had significantly lower levels of traumatic stress symptoms, depression, anxiety and functional impairment at post-treatment and one month follow-up, in comparison to the delayed treatment group, who improved to the same degree after receiving GSH for PTSD. Results of the development and pilot work indicated a strong rationale for conducting a larger scale RCT to determine whether GSH represents a treatment option that should be routinely used in the care of PTSD sufferers, as it is for depression and numerous anxiety disorders.

A Cochrane review of RCTs of online GSH for PTSD in comparison to face-to-face therapy, waitlist or usual care [29] found two previous studies [30, 31]. The first compared online GSH with 104 min of guidance to a waitlist in 42 adults with PTSD [30]. A large within group effect size was found in the GSH group from pre- to post-treatment for self-reported PTSD symptoms (Cohen’s d = 1.18) but a smaller between groups effect size was found post-treatment, due to symptom improvement in the control group. The second RCT compared online GSH to a delayed treatment minimal attention group in 62 PTSD sufferers [31]. A larger between group effect size of d = 1.25 was found. The interventions included in both studies were largely text-based and may not have been optimal in terms of usability. The online GSH intervention developed by this study team includes audio and video clips and is therefore more interactive which may explain the positive results seen in the pilot study.

The review demonstrated that there have been no comparative trials of online GSH and face-to-face therapy to date, precluding firm decisions being made on whether to deliver GSH for PTSD as an alternative to face-to-face therapy in the NHS. The proposed study will address this by generating high quality scientific evidence for an intervention already developed by us through state of the art methodology. Our aim is to test online GSH as a treatment for adults who have been exposed to a single traumatic event. The primary objective of the trial is to determine: Whether an online TFCBT based GSH programme is not inferior to individual TFCBT for patients with PTSD as judged by reduced symptoms of PTSD at 16 weeks post-randomisation, thus enabling decisions to be made about its suitability for use in the NHS. The secondary objectives of the trial are to determine:Whether an online TFCBT based GSH programme is not inferior to individual TFCBT for patients with PTSD as judged by reduced symptoms of PTSD at 52 weeks post-randomisation.Whether an online TFCBT based GSH programme is not inferior in effectiveness to individual TFCBT for patients with PTSD as judged by improved quality of life at 16 weeks and 52 weeks post-randomisation.The impact of an online TFCBT based GSH programme on functioning, symptoms of depression, symptoms of anxiety, symptoms of PTSD, alcohol use, insomnia, perceived social support, self-efficacy and cognitions for people with PTSD at 16 weeks and 52 weeks post-randomisation.Whether an online TFCBT based GSH programme is cost-effective relative to individual TFCBT for patients with PTSD at 16 weeks and 52 weeks post-randomisation.The factors which may impact effectiveness and successful roll-out of online GSH for PTSD in the NHS if the GSH programme is shown to be effective.

## Methods/design

The design is that of a multi-centre pragmatic randomised controlled non-inferiority trial with assessors masked to treatment allocation. Individual randomisation will be used.

### Study setting

The trial will take place in NHS Improving Access to Psychological Therapy (IAPT) services based in primary care in England, and in NHS psychological treatment settings based in primary and secondary care in Scotland and Wales. The sites cover urban and rural, economically and non-economically deprived areas of the UK in Coventry, Warwickshire, Greater Manchester, London, South West Yorkshire, South Wales and Lothian.

### Eligibility criteria

Wide eligibility criteria will be used to ensure good external validity. Given the high rate of co-morbidity of PTSD and other conditions such as depression and substance misuse, individuals with co-morbidity will be included if they satisfy the other inclusion/exclusion criteria and PTSD is considered the primary diagnosis. This is consistent with NICE guidance for the treatment of PTSD [12] and will result in a pragmatic trial. See Table 1 for Inclusion and Exclusion Criteria.

**Table 1 Tab1:** RAPID Inclusion and Exclusion Criteria

*Inclusion Criteria*
Participants must be:
1) Aged 18 or over
2) Screen positive for PTSD to a single traumatic event on the Trauma Screening Questionnaire (TSQ)
3) Have regular access to the internet in order to complete the steps and homework required by the GSH programme
4) Be willing and able to give informed consent to take part
5) After a 2 week monitoring period, continue to meet CAPS-5 criteria for mild to moderate PTSD (score less than 50)
6) Have PTSD as their primary diagnosis.
*Exclusion Criteria*
A person is not eligible to enter the trial if any of the following apply (all of these are measured via self-report):
1) Inability to read and write fluently in English
2) Previous completion of a course of TFPT for PTSD
3) Currently engaged in a psychological therapy
4) Change in psychotropic medication in the last 4 weeks
5) Psychosis
6) Substance dependence
7) Active suicide risk

With reference to inclusion criterion 2, previous work with more complex and severe forms of PTSD, e.g. following prolonged and repeated trauma suggests that it often requires increased therapist time and is therefore less likely to be effectively treated by GSH [12]. In terms of criterion 5, symptoms can remit when monitored, hence the 2 week self-monitoring period in which participants will be asked to complete a simple daily diary of symptoms at home [32, 33]. Participants cannot engage in concurrent psychological therapy whilst in the trial. They can continue taking psychotropic medication but are not eligible if they have had a change in medication 4 weeks prior to being assessed.

### Interventions

The trial will compare online GSH against individual face-to-face TFCBT, which is current standard care in the sites taking part in the trial.

#### TFCBT for PTSD

TFCBT for PTSD is one of the standard treatments adopted by IAPT in England and has been shown to be effective in RCTs in England [11, 33–36] and Northern Ireland [37]. There are a number of evidence based TFCBTs and, given the pragmatic nature of the trial, it will be permissible to use any one of them with individuals allocated to the TFCBT arm. An example of an evidence-based TFCBT is cognitive therapy for PTSD (CT-PTSD). CT-PTSD involves identifying the relevant appraisals, memory characteristics, triggers, and behavioural and cognitive strategies that maintain PTSD symptoms. CT-PTSD addresses these symptoms by: 1) Modifying excessively negative appraisals of the trauma and/ or its sequelae, 2) Reducing re-experiencing by elaboration of the trauma memories and discrimination of triggers, 3) Dropping dysfunctional behaviours and cognitive strategies, particularly those related to avoidance of triggers for intrusive symptoms. These are strategies that have the immediate aim of reducing one’s sense of current threat but have the long-term effect of maintaining the disorder, and are common in PTSD.

In this study, TFCBT will be delivered by experienced psychological therapists currently working in the IAPT or psychological services. They come from a variety of backgrounds, including mental health nurses, clinical psychologists and counsellors, and have varying levels of experience in working therapeutically with people with PTSD. All therapists will attend at least 1 one-day workshop on one of the TFCBT programmes. In addition, all study therapists are required to attend at least one and a half days training in CT-PTSD delivered by the group who developed CT-PTSD and to be assessed as being at least satisfactorily competent in the delivery of TFCBT by one of the two supervising authors who are experienced in TFCBT (NK, NR). The therapists will be given a treatment manual and will receive supervision once per month from one of two authors (NK, NR).

TFCBT will be delivered face-to-face to individual participants over the course of up to 12 sessions, each lasting 60–90 min. Appointments will take place at the service base. In-session treatment is augmented by daily homework assignments which participants are required to complete between sessions. They will be asked to complete the Impact of Events Scale-Revised (IES-R) at each session to measure and monitor their PTSD symptoms.

#### Spring: An internet based guided self-help Programme for PTSD

Spring is an online GSH programme based on TFCBT. It uses the same principles as TFCBT but aims to reduce contact time with the therapist by providing some of the therapy content and activities in an accessible self-help format. Potential advantages include that the service user can engage in the intervention at a time and place convenient to them which may reduce drop out, and it may also reduce waiting list times as it should reduce the input time required for therapist.

The expectation is that Spring will be delivered by the same therapists delivering the TFCBT. All the therapists will receive a half day’s training from two of the authors who were involved in developing the intervention and delivering it in the pilot study (NK, NR). Therapists also receive ongoing supervision of one or more training cases until they are regarded as competent. The therapists will work from a manual and, for the duration of the trial, will receive supervision once per month from NK or NR.

Spring is an 8 week online program comprising eight steps (see Table 2. Spring PTSD Steps).

**Table 2 Tab2:** Spring PTSD Steps

Step 1: Learning About My PTSD – Psychoeducation about PTSD illustrated by four actors describing their experience of PTSD to different types of traumatic event.
Step 2: Grounding Myself - Explanation of grounding and its uses along with descriptions and demonstrations of grounding exercises.
Step 3: Managing My Anxiety – Education about relaxation techniques with learning through videos of a controlled breathing technique, deep muscular relaxation and relaxation through imagery.
Step 4: Reclaiming My Life – Behavioural re-activation to help individuals return to previously undertaken/new activities.
Step 5: Coming to Terms with My Trauma – Provides rationale for imaginal exposure, narratives of the four video characters. The therapist helps the participant to begin writing a narrative, which they complete remotely and read every day for at least 30 min.
Step 6: Changing My Thoughts – Cognitive techniques to address PTSD symptoms.
Step 7: Overcoming My Avoidance – Graded real life exposure work.
Step 8: Keeping Myself Well – This session reinforces what has been learnt during the programme, provides relapse prevention measures and guidance on what to do if symptoms return.

The therapist initially meets with the participant at the service base for an hour to develop a rapport, learn about the participant’s trauma and describe the programme, which the participant then completes online in their own time. There are four subsequent fortnightly meetings of 30 min, normally undertaken face-to-face, but potentially deliverable via the internet or telephone, according to participant preference. The participant will also receive four brief telephone calls or email contact between sessions to discuss progress, identify any problems that have arisen and sometimes set new goals. The modules are accompanied by homework. At each session, the therapist reviews progress by logging into a clinician dashboard, and guides the participant through the programme. The aim of the guidance is to offer continued support, monitoring, motivation and problem solving. The eight online steps are usually completed in turn with some later steps relying on mastery of techniques taught in earlier steps. Each step provides psycho-education and the rationale for specific components of treatment. Each step activates a tool that becomes live in the Toolkit area of the website and aims to reduce traumatic stress symptoms. Everything entered into the Toolkit becomes visible (with the participant’s knowledge) to the therapist via the dashboard to facilitate input. The programme can be accessed online via a web browser or through an App. Participants will be able to use their PCs, tablets or smart phones to engage with the programme. A screenshot taken from Step 1 can be seen in Fig. 1: Spring Screenshot. Participants will be asked to complete the IES-R at each face-to-face session to measure and monitor their PTSD symptoms.

**Fig. 1 Fig1:**
[figure not shown]
Spring Screenshot. A screenshot, taken from Step 1, showing the actors whose PTSD case histories are followed throughout the intervention. The Toolkit can be seen at the bottom of the webpage

### Participant withdrawal

A participant may withdraw or be withdrawn from either intervention for the following reasons: 1) Withdrawal of consent to participate in the intervention by the participant, 2) Any alteration in the participant’s condition which justifies the discontinuation of the intervention in the therapist’s/Principal Investigator’s opinion. For example, developing a condition which would exclude them from the study based on the eligibility criteria.

In the case of suicidal ideation, the therapist will assess the participant to determine whether or not they can continue or need to be referred elsewhere. In the case that a participant scores 50+ on the CAPS-5 at follow-up, they will also need to be assessed by the clinical team and may be offered additional treatment. Participants who solely withdraw/are withdrawn from the intervention will continue in follow-up unless they withdraw their consent for this.

Participants can chose to withdraw from the trial intervention, withdraw from follow-up, withdraw from both aspects, or withdraw from both aspects and ask that previously collected data not be used.

### Fidelity

To ensure the interventions are delivered as intended and according to the manuals, each therapist will aim to audio record at least one session with every participant using a digital recorder (however, this may not be pragmatic for GSH if the sessions are solely conducted on the telephone or by email). The audio recordings will be rated using a general and an intervention specific fidelity checklist by one of two independent raters, who have received training in the intervention. We will record the number of sessions attended or missed for each participant, and the time spent on the GSH programme to measure adherence.

### Outcomes

The primary outcome will be the severity of symptoms of PTSD over the previous week as measured by the Clinician Administered PTSD Scale for DSM5 (CAPS-5) [38] at 16 weeks post-randomisation. The CAPS-5 is a 30 item structured interview for assessing PTSD diagnostic status and symptom severity. It is the gold standard in PTSD assessment and can be used to make a current (past month) or lifetime diagnosis of PTSD or to assess symptoms over the past week. Items correspond to the DSM5 criteria for PTSD. Previous versions of the CAPS have excellent reliability and convergent and discriminant validity, diagnostic utility, and sensitivity to clinical change [39]. Sixteen weeks was chosen as a post-intervention measurement.

Secondary outcomes include the severity of PTSD symptoms at 52 weeks post-randomisation to determine whether any effects of the intervention are sustained, and will be measured using the CAPS-5 1 month version. Other secondary outcomes to be measured at both 16 weeks (to determine the effect of the intervention) and 52 weeks post-randomisation (to determine sustained effects) will include symptoms known to be commonly associated with PTSD along with functional status. To assess these, we will use self-report measures that are routinely collected by IAPT services: 1) Traumatic stress as measured by the Impact of Event Scale – revised [40], 2) Quality of Life/functional impairment as measured by the Work and Social Adjustment Scale [41], 3) Depression measured by the Patient Health Questionnaire-9 [42], 4) Anxiety measured by General Anxiety Disorder-7 [43] and 5) Alcohol use measured by AUDIT-O [44].

Additional, non-IAPT measures will be administered at 16 and 52 weeks post-randomisation. Perceived social support will be measured using the Multidimensional Scale for Perceived Social Support [45], and the level of healthcare resource utilisation for health economic analysis will be determined by an amended version of the Client Socio-Demographic and Service Receipt Inventory European Version [46]. Changes in health related quality of life will be measured by the EQ-5D [47] and changes in sleep measured by the Insomnia Severity Index [48]. A short version of the Post-Traumatic Cognitions Inventory [49] and the General Self Efficacy Scale [50] will be collected to determine effects on cognitions and self-efficacy respectively. The Client Satisfaction Questionnaire [51] will be collected at 16 weeks post-randomisation only, to evaluate treatment satisfaction.

The IES-R will be collected at each therapy contact to provide clinical feedback and also to facilitate imputation for missing data, if required. How frequently it is collected will depend on the frequency of therapist contact, but is likely to be weekly in the TFCBT arm and fortnightly in the GSH arm.

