To aid retention, participants will be offered a £10 shopping voucher on completion of the 16 week and 52 week follow-up assessments as a token of appreciation for their participation in the study. Where a participant wishes to withdraw from the intervention, their participation in the follow-up assessments will be encouraged. Unless a participant has withdrawn consent for follow-up, repeated attempts using different approaches will be made to contact participants who cannot be easily contacted. In a step-wise manner, this will involve checking contact details with their study therapist, calling the individual on all contact numbers provided on various days of the week and at different times, sending emails and a letter to the addresses provided. If contact can still not be made, the individual’s GP will be contacted to check contact details are correct. If these attempts do not result in contact being made within 1 month of loss of contact or the planned follow-up, a letter will be sent asking the participant to re-establish contact if they are able to and advising that they will be contacted again at the next follow-up point unless they advise otherwise. For any participant reluctant to complete the full outcome assessment at follow-up we will attempt to gain the CAPS-5 information as a minimum dataset. As much information as possible will be collected from protocol non-adherers, with a minimum of the primary and secondary outcome measures and reasons for non-adherence.

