### Statistical methods

The primary analysis will be performed using analysis of covariance, predicting follow-up CAPS-5 score controlling for baseline CAPS-5 score and important patient characteristics (including all minimisation variables). This will be a complete case intention to treat analysis. Checks will be made to ensure there is no appreciable clustering of outcomes within therapists, but if such clustering exists the primary analysis will be hierarchical. The results will be summarised using point estimates, 95% confidence intervals and *p*-values. Since this is a non-inferiority design, we will be checking whether the confidence interval for the difference between arms lies entirely within the 5 point non-inferiority margin. Participants with missing CAPS-5 score at follow-up will have a CAPS-5 score estimated from available IES-R scores (this will involve building a prediction model using information from participants with both IES-R and CAPS-5 scores). We will explore differences in treatment effects by gender in a sub-group analysis by including an interaction term between treatment arm and gender.

A sensitivity analysis will use multiple imputation to account for missing data if the number of cases lost due to incomplete information exceeds 10%. Secondary outcomes include: CAPS-5 at 52 weeks, IES-R, WSAS, PHQ-9, GAD-7, AUDIT-O, MSPSS, EQ-5D, ISI, GSES, PTCI, adapted CSSRI-EU and CSQ-8. These are all continuous measures and will be analysed similarly to the primary outcome. Transformations will be explored to improve model fit if distributional assumptions are not satisfied. This will be assessed by visual inspection and formal fit statistics compared to decide on the transformation chosen.

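### A participant who misses the 16-week assessment loses both the CAPS-5 and the IES-R meant to replace it, leaving earlier IES-R scores whose timing differs by arm

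*Protocol article*

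**What the plan says.** All references are to the protocol article.

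- **Use of the IES-R.** Statistical methods says that a missing follow-up CAPS-5 will be predicted from available IES-R scores, with a model built on participants who have both.
- **Collection during therapy.** Outcomes: "The IES-R will be collected at each therapy contact to provide clinical feedback and also to facilitate imputation for missing data, if required". The same paragraph expects that the frequency "is likely to be weekly in the TFCBT arm and fortnightly in the GSH arm". The section on the Spring programme is narrower: "Participants will be asked to complete the IES-R at each face-to-face session". It also allows the four later GSH meetings to be held by internet or telephone.
- **Collection at follow-up.** The IES-R is also an outcome measure in its own right. Outcomes introduces "Other secondary outcomes to be measured at both 16 weeks (to determine the effect of the intervention) and 52 weeks post-randomisation" and lists first "Traumatic stress as measured by the Impact of Event Scale". Statistical methods agrees: "Secondary outcomes include: CAPS-5 at 52 weeks, IES-R, WSAS, PHQ-9". Data Collection Methods & Data Management has assessors repeat the outcome measures at 16 and 52 weeks, with self-report forms completed during the assessment.
- **Minimum data.** For a participant reluctant to do the full follow-up assessment, "we will attempt to gain the CAPS-5 information as a minimum dataset". For those not adhering to the protocol, as much as possible is collected, "with a minimum of the primary and secondary outcome measures and reasons for non-adherence".

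**The concern.** A fallback measure is useful only if it tends to be present when the main measure is absent. Here the two are taken together at week 16, so a missed assessment normally removes both. The tracing steps are detailed (therapist, telephone, email, letter, GP), but none of them asks for the short self-report IES-R alone when the interview cannot be arranged.

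The prediction for such a participant would then rest on scores from baseline and therapy. These describe an earlier state, and by design they are spaced differently and probably end at different times in the two arms. Any error from the time lag could therefore differ between arms and enter the treatment difference that is compared with the 5-point margin. This is a question of which data exist. A statistical analysis plan can choose how to use the scores, but cannot restore scores that were never taken.

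**Working it through.** **1. How many participants could be affected.** Inputs from Sample size: 186 before inflation, cluster size 4, clustering 1%, attrition 20%.
- Design effect: 1 + (4 − 1) × 0.01 = 1.03. Then 186 × 1.03 = 191.6, which rounds up to the stated 192. The total is not in dispute.
- Allowed attrition: 192 × 0.20 = 38.4, about 38 participants. With 1:1 allocation this is about 19 per arm if losses are equal.
- This is an upper bound under the plan's own allowance.

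**2. When the last in-therapy score falls.** Assumption: therapy starts at randomisation and runs to schedule. The article fixes no start date.
- GSH: a first meeting and four more at two-week intervals, so weeks 0, 2, 4, 6 and 8. Gap to the outcome: 16 − 8 = 8 weeks.
- TFCBT: up to 12 sessions, expected weekly, so weeks 0-11 or 1-12. Gap: 16 − 11 = 5 or 16 − 12 = 4 weeks.
- Difference in gap between arms: 3 to 4 weeks for participants who complete therapy. For those who stop early the gap is longer in either arm, and the difference between arms depends on when they stop.

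**3. What the conflicting GSH wording implies.** Number of in-therapy IES-R scores for one GSH participant who attends everything:

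| Rule applied | Scores |
|---|---|
| Every therapy contact (meetings plus the four calls or emails between them) | 1 + 4 + 4 = 9 |
| Fortnightly, at the scheduled meetings | 1 + 4 = 5 |
| Face-to-face only, all later meetings remote | 1 |

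The first two rows both come from Outcomes, which speaks of every contact but expects a fortnightly frequency. The third follows from the Spring section. The ambiguity falls on the GSH arm alone.

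**4. Effect on the treatment difference (illustration only).** Shift = share missing × between-arm difference in the error of the filled scores. The document gives no value for that difference; 1 to 8 points is an assumed range. The formula takes equal missing shares in both arms and every missing score filled from pre-week-16 data.

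| Share missing | 1 point | 3 points | 5 points | 8 points |
|---|---|---|---|---|
| 10% | 0.1 | 0.3 | 0.5 | 0.8 |
| 20% | 0.2 | 0.6 | 1.0 | 1.6 |

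Against the 5-point margin this spans 0.1/5 = 2% to 1.6/5 = 32%. The table shows how an error would carry through. It is not evidence that one of a given size exists.

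**The case against.** Several stronger readings are tempting, and the document does not support them.

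- *That the IES-R is collected only while therapy lasts.* It is a 16- and 52-week outcome as well.
- *That people who stop treatment have only an early score.* Participant withdrawal keeps them in follow-up unless they withdraw consent for it, and their follow-up assessments are encouraged. Only those with no 16-week assessment are affected.
- *That the IES-R is left out of the minimum follow-up data.* The minimum for non-adherers covers the secondary outcomes and so includes it. The CAPS-5-only minimum applies to reluctant participants, and where it is obtained there is nothing to fill. The two minima address different situations; nothing says that these are the same people.
- *That GSH participants will often have a single score.* The Spring section describes the meetings as normally face-to-face, and Outcomes expects fortnightly scores. One score is the extreme case.

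It can also be said that lag alone does not prove bias. A model that relates earlier IES-R to 16-week CAPS-5 can allow for average later change, and the choice of time points and any window may properly be left to the statistical analysis plan. A multiple-imputation sensitivity analysis is planned if losses exceed 10%.

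All of this stands, and it narrows the point. It does not remove it: no step seeks the IES-R alone when the interview fails, the in-therapy schedules differ by arm, and the two statements on GSH collection cannot both be followed when meetings are remote.

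**Conclusion.** The point holds for participants with no 16-week assessment. For them the planned prediction would usually rest on baseline and in-therapy IES-R, which predate week 16 and differ by arm in frequency and probably in last date (about week 8 under GSH, week 11-12 under TFCBT). The timing rests on therapy starting at randomisation and keeping to schedule. At most about 38 participants are concerned. The size and direction of any bias are unknown, and no figure in the document is shown to be wrong. The conflict between Outcomes and the Spring section on GSH collection is a plain inconsistency and holds without assumptions.

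The change is worth making because it is cheap and determines which data will exist for the primary non-inferiority comparison.

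**What to change.** 1. **Data Collection Methods & Data Management.** Add that, when the CAPS-5 interview cannot be obtained and consent to follow-up has not been withdrawn, the self-report IES-R is sought on its own at weeks 16 and 52. Use the letters, emails and telephone calls already in the tracing sequence, and record the completion date.
2. **Outcomes and the Spring section.** Reconcile the two so that the IES-R is collected at every scheduled GSH meeting, whether face-to-face, by internet or by telephone.

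Which IES-R time points enter the prediction, any time window, and the use of session scores as auxiliary variables can stay with the statistical analysis plan.

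The cost is protocol wording, one short form in mailings that are already planned, and slightly more contact with hard-to-reach participants. An online link for participants should not be assumed to be free: database access is limited to named study staff, so paper, email or telephone completion is the simpler route. The step will not reach those who answer no contact at all, so it reduces the problem without removing it.
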